## Abstract

**Background:**

Although clozapine is the most effective antipsychotic drug for treatment-resistant schizophrenia, it leads to a poor or partial response in 40 to 70% of patients. Augmentation of clozapine with electroconvulsive therapy (ECT) is a highly effective and relatively safe treatment for these clozapine-resistant patients. However, parameters are not yet well specified, such as the optimal number of sessions, their frequency, and the relevance of maintenance ECT. Our objective is to compare the efficacy and tolerance between two protocols of combined ECT and clozapine treatment in patients with ultra-resistant schizophrenia (URS): a 6-month protocol (short protocol with 20 ECT sessions) and a 12-month protocol (long protocol with 40 ECT sessions).

**Methods:**

Sixty-four patients with schizophrenia with persistent psychotic symptoms despite clozapine treatment will be enrolled in a prospective multicentric assessor-blinded randomized controlled trial. Patients will be randomly assigned to the short or the long protocol. The main outcome is the response rate assessed by the Positive and Negative Symptoms Scale (PANSS) 3 months after the end of the treatment in patients following the long protocol compared to those following the short protocol. The response was defined as a 30% reduction on the PANSS baseline. Clinical assessments (PANSS, BPRS, HAMD-21, YMRS, CGI, GAF, Modified Overt Aggression Scale (MOAS), and Subjective Scale to Investigate Cognition in Schizophrenia (SSTICS)) and plasma clozapine concentration will be performed at baseline and at 2, 4, 6, 9, 12, and 15 months. Neuropsychological measures (MMSE, RL/RI-16, Doors test, D2 Test of Attention, Copy of the Rey-Osterrieth complex figure) will be performed at baseline and at 6 and 15 months.

**Discussion:**

The aims of this research are to optimize protocols of combined ECT with clozapine in patients with URS and to offer specific recommendations for these patients’ care.

**Trial registration:**

ClinicalTrials.gov NCT03542903. Registered on May 31, 2018. Id RCB: 2017-A02657-46

## Introduction

### Background and rationale {6a}

Treatment-resistant schizophrenia (TRS) is a severe disorder with little to no response to antipsychotic drugs, affecting about 10 to 30% of patients with schizophrenia [1]. The lack of response to antipsychotics is associated in these patients with the worst community functioning among severely ill highly disabling psychiatric disorders, i.e., TRS, schizophrenia responsive to antipsychotics, bipolar disorder, anxiety/depressive diseases [2]. Suffering from persistent psychotic symptoms and cognitive dysfunctions, these patients with TRS manifested the poorest functioning in everyday life, being for the great majority unemployed and having not their own home [2]. Although clozapine is known to be the most effective antipsychotic drug in those cases, it leads to a poor or partial response in 40 to 70% of patients [3], and these patients are considered to have “ultra-resistant schizophrenia” (URS).

According to a recent meta-analysis of 18 randomized controlled trials comprising 1769 patients, ECT augmentation of clozapine had superior efficacy to clozapine as a monotherapy, was safe and relatively well tolerated by clozapine-resistant patients [4]. However, 17 of the 18 studies included in the meta-analysis were in Chinese, not allowing us to judge their scientific quality. Only one methodologically sound study was published in English by Petrides et al. [5]. In this prospective randomized study, 39 patients with clozapine-resistant schizophrenia were assigned either in the “ECT plus clozapine” group (*n* = 20) or in the “clozapine” group (*n* = 19). In the intent-to-treat analysis, ten of the 20 patients (50%) in the ECT augmentation group but none of the patients (0%) in the clozapine group met the response criterion. The response was defined as a 40% reduction in symptoms based on the psychotic symptom subscale of the Brief Psychiatric Rating Scale (BPRS), a Clinical Global Impressions (CGI)-severity rating of mild or less (less than 3), and a CGI improvement rating of much improved (less than or equal to 2). Augmentation of clozapine with ECT is therefore an extremely promising therapeutic strategy for patients suffering from URS, but there is a lack of randomized controlled trials investigating important methodological aspects such as the optimal number and frequency of sessions as well as the need for maintenance ECT. For example, it seems that a larger number of ECT sessions is required in patients with TRS than in depression [6], but without real experimental evidence. In fact, the duration of most studies about ECT in URS patients is relatively short (between 4 and 6 months), and a high relapse rate was reported in the weeks to months after ECT cessation [7]. In order to decrease the risk of relapse, some experts empirically recommended ECT protocols with a duration ranging from 6 to 12 months. To our knowledge, advantages and disadvantages of a short versus a long treatment protocol have never been investigated. In this context, we designed a prospective randomized controlled trial in order to compare the effects of two different duration protocols of combining ECT with clozapine in URS patients.

### Objectives {7}

Our main objective is to compare the efficacy between two combined ECT-clozapine protocols in patients with ultra-resistant schizophrenia (URS): a 6-month protocol (short protocol with 20 ECT sessions) and a 12-month protocol (long protocol with 40 ECT sessions).

We hypothesize that the long protocol will be more effective than the short protocol 3 months after the end of the treatment.

In the second aim, we will compare the effects of both protocols on clinical symptomatology throughout the study. We hypothesize that the clinical improvement will be superior in the long protocol than in the short protocol.

Finally, we will compare the impact of both protocols on cognition. We hypothesize that the cognitive side effects will be similar between the two groups, except for attention, the improvement of which would be greater in the long protocol. We assume indeed that the greatest clinical improvement expected in the long protocol can induce an attention enhancement.

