### Trial design {8}

This study is a prospective, multicentric, randomized, two-arm, assessor-blinded trial.

Due to the severity of the patients’ condition, it is not ethically possible to conduct sham ECT sessions, making the blinding about the short or long arm impossible to maintain in patients. In this superiority trial, patients will be randomly assigned to one of both arms with an allocation ratio of 1:1.

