#### Secondary outcomes

The secondary outcomes are as follows:
The response rate assessed by the Brief Psychiatric Rating Scale-18 items (BPRS-18) 3 months after the end of the treatment in patients following the long protocol compared to those following the short protocol (the response being defined as a reduction of 30% on the BPRS).The response rates assessed by the PANSS and the BPRS at different times (2, 4, 6, and 12 months) between both groups.The Hamilton Rating Scale-21 items (HAMD-21) score, the Young Mania Rating Scale (YMRS) score, the Modified Overt Aggression Scale (MOAS) score, the Clinical Global Impression (CGI) score, and the Global Assessment Functioning (GAF) score at baseline and at 2, 4, 6, 9, 12, and 15 months. Changes from baseline will be compared between both groups.The Mini-Mental Status Examination (MMSE), the Subjective Scale to Investigate Cognition in Schizophrenia (SSTICS) [13], the RL/RI-16 test assessing verbal memory [14], the Doors test assessing visual memory [15], the D2 Attention Test [16], and the Copy of the Rey-Osterrieth Complex figure test for the evaluation of visuospatial constructional ability [17] at baseline and at 6 and 15 months. Changes between baseline and 6 months and between baseline and 15 months will be compared between the groups.Plasma clozapine concentration measured at baseline and at 2, 4, 6, 9, 12, and 15 months in order to check patient compliance.

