### Sample size {14}

The aim of this trial is to compare the response rates between short and long ECT protocols. According to the meta-analysis of Lally et al. [7], the proportion of patients with treatment-resistant schizophrenia that responds to ECT augmentation of clozapine was 61.79% (Table 1: 55/89 cases). However, the relapse following ECT cessation is very high: the relapse rate has been estimated at 62.5% by Kho et al. [18]. On the other hand, Braga et al. [19] suggested that ECT were effective as a continuation strategy to prevent relapse after an acute course of ECT. During the 6-month maintenance period, no patient presented with clinically worsening symptoms. From this literature data, we postulate that the responder rates would be 61.79% in the long ECT protocol and 23.25% in the short ECT protocol (62% × (1 − 0.625) = 23.25%). Assuming an alpha risk of 0.05 and a power of 0.80, we estimated the need to include 25 patients per group. To overcome an estimated 20% drop-out, the required number of patients increased to 32 patients per group. As a result, the total number of participants required for the study is 64 patients.

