## Statistical methods

### Statistical methods for primary and secondary outcomes {20a}

Patient characteristics will be described overall and by randomly allocated treatment arm (short or long therapy) using the usual parameters, i.e., mean, standard deviation, median, interquartile range, and range for quantitative characteristics and frequencies for categorical characteristics.

The main outcome (the response rate in the PANSS three months after treatment cessation) being categorical, Pearson’s chi-square test will be used. The same strategy will be applied for the other categorical criteria (secondary outcomes). For the secondary outcomes with quantitative measures, the comparison between both groups will be performed thanks to the repeated measures ANOVA or Mann-Whitney tests based on delta scores (i.e., month 6 minus baseline, month 15 minus baseline), when the assumptions of variance equality and/or normal distribution are violated. If multiple Mann-Whitney tests are performed, Bonferroni adjustment will be applied to compensate for the risk of type 1 errors.

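### Cognitive side effects are hypothesised to be similar, but the plan provides only tests for a difference, so a non-significant result cannot support the hypothesis

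*Protocol article*

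**What the plan says.** Under Objectives {7}, the third aim concerns cognition: "We hypothesize that the cognitive side effects will be similar between the two groups, except for attention". For attention, a greater improvement is expected in the long arm. Trial design {8} describes a superiority trial with 1:1 allocation and mentions no equivalence or non-inferiority component.

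Secondary outcomes {12} lists six instruments under cognition (MMSE, SSTICS, RL/RI-16, Doors, D2, copy of the Rey figure), to be given at baseline and at months 6 and 15. It adds: "Changes between baseline and 6 months and between baseline and 15 months will be compared between the groups".

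The statistical methods section {20a} gives one approach for all quantitative secondary outcomes: "the comparison between both groups will be performed thanks to the repeated measures ANOVA or Mann-Whitney tests based on delta scores", the second option applying when the ANOVA assumptions fail. On multiplicity it says: "If multiple Mann-Whitney tests are performed, Bonferroni adjustment will be applied to compensate for the risk of type 1 errors". The article gives no margin and no confidence-interval rule for cognition. The only sample size calculation {14} is for PANSS response.

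**The concern.** Similarity is a claim that a difference is small. It needs a statement of how small, and an interval that excludes anything larger. A test of no difference can reject similarity but cannot establish it, because a non-significant p-value may reflect either a small effect or too few patients. Here the article itself pairs the similarity hypothesis with difference tests only, so the mismatch is not just a detail deferred to another document.

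Bonferroni protects against falsely declaring a difference. On a harm question where no difference is the expected result, that protection works in favour of the expectation.

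The Abstract gives the objective as comparing efficacy and tolerance. The Discussion calls cognitive impairment a frequent result of ECT and says its effect after very long series is not known. A reader choosing between 20 and 40 sessions needs to know how much cognitive harm the trial has ruled out, and the planned tests do not report that.

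**Working it through.** **The plan's own figure.** "we postulate that the responder rates would be 61.79% in the long ECT protocol and 23.25% in the short ECT protocol". With the pooled-variance formula, two-sided alpha 0.05 and power 0.80, the mean rate is 0.4252, and

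n = [1.960·√(2·0.4252·0.5748) + 0.842·√(0.6179·0.3821 + 0.2325·0.7675)]² / 0.3854² ≈ 24.6, so 25 per arm; 25/0.80 = 31.25, so 32 per arm.

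This agrees with the article. It says nothing about power for cognition.

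**Inputs for cognition.**
- n = 25 per arm (evaluable) or 32 per arm (randomised), from Sample size {14}.
- Two-sided alpha 0.05, or 0.05/k with Bonferroni over k tests. The article does not state k.
- Illustrative values of k: 2 (two changes for one measure) and 10 (five non-attention instruments, one score each, times two changes).
- True deficit d in units of the SD of change. This is an assumption; 0.5 and 0.8 are shown.

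**Formula (normal approximation).** Chance of a significant result ≈ Φ(d/√(2/n) − z), with z = 1.960 for k = 1, 2.241 for k = 2 and 2.807 for k = 10. √(2/n) is 0.283 for n = 25 and 0.250 for n = 32. The miss rate is one minus this.

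For d = 0.5 and k = 1:
- n = 25: 0.5/0.283 = 1.77; Φ(1.77 − 1.96) = 0.42; missed 58%.
- n = 32: 0.5/0.250 = 2.00; Φ(2.00 − 1.96) = 0.52; missed 48%.

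| True deficit | Tests in Bonferroni family | Missed, 25 per arm | Missed, 32 per arm |
|---|---|---|---|
| 0.5 SD | none | 58% | 48% |
| 0.5 SD | 2 | 68% | 60% |
| 0.5 SD | 10 | 85% | 79% |
| 0.8 SD | none | 19% | 11% |
| 0.8 SD | 10 | 49% | 35% |

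The noncentral t lowers power by 0 to 5 points, and a Mann-Whitney approximation (efficiency 0.955) by up to 3 more, so the miss rates are if anything slightly low. The ANOVA group-by-time test also depends on within-patient correlations that the article does not give.

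**What an interval would show.** The 95% CI half-width for a difference in change is t·√(2/n): 0.57 SD of change at 25 per arm and 0.50 at 32. If the true difference is zero, the chance that the interval excludes a deficit of 0.5 SD of change is Φ(0.5/√(2/n) − 1.96) = 42% or 52%. For 0.8 SD it is 81% or 89%.

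Baseline adjustment multiplies the outcome SD by √(1 − r²). With r assumed at 0.6 to 0.8, the half-width is 0.30 to 0.46 SD of the outcome across the two sample sizes. At r = 0.7 the chance of excluding 0.5 outcome SD is about 70% (25 per arm) or 80% (32 per arm).

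**Units matter.** With equal variances, SD of change = baseline SD·√(2(1 − r)). A deficit of 0.5 baseline SD is then 0.5/0.894 = 0.56 SD of change at r = 0.6 and 0.5/0.632 = 0.79 at r = 0.8. The unadjusted miss rate for it is 49% to 20% at 25 per arm and 39% to 12% at 32.

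**Timing.** The short course ends at about month 6 and the long course at about month 12. At the month-6 assessment the short course is ending while the long course continues. At month 15 the arms are 15 − 6 = 9 and 15 − 12 = 3 months past ECT. The primary outcome is matched at 3 months after treatment; neither cognitive contrast is matched in this way.

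**The case against.** Several stronger readings are tempting, and the article does not support them.

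- A reader might infer that a non-significant test will be reported as similar. No such rule is written. The Objectives state an expectation and the Outcomes section says only that changes will be compared.
- A reader might take Bonferroni as always in force. It applies only if several Mann-Whitney tests are run, which is the fallback; the ANOVA carries no stated adjustment. The size of the family is not given, and a count of 12 would include the D2 attention test, which is exempt from the similarity hypothesis.
- A reader might conclude that the trial can only fail to find harm. That is false: an unadjusted test detects a 0.8 SD deficit in about 81% (25 per arm) or 89% (32 per arm) of trials. Even at 0.5 SD and 32 per arm, the unadjusted test finds it slightly more often than not.

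It can also be said that cognition is a secondary outcome, that a margin and a multiplicity family are commonly left to an analysis plan, and that the timing asymmetry is visible from the schedule. All of this is fair. The timing is a matter for interpretation and not an error; shorter recovery in the long arm at month 15 would, if anything, make harm more visible. What remains is that the article itself fixes difference tests for a hypothesis of similarity, and these cannot support it.

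**Conclusion.** The point holds in this form: the stated tests cannot support the stated hypothesis for cognitive measures other than attention, and the conditional Bonferroni rule, if triggered, makes a null result on harm easier to reach. Moderate harm could well be missed: 58% or 48% of the time for 0.5 SD of change unadjusted, and 68% to 85% or 60% to 79% with Bonferroni over 2 to 10 tests (25 or 32 per arm). Large harm would usually be found without adjustment. These rates rest on assumed effect sizes, one score per instrument, assumed family sizes and a normal approximation. The mismatch between hypothesis and test does not depend on them. It affects a secondary objective and leaves the primary analysis untouched.

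**What to change.** For each cognitive measure other than attention:

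- Report the baseline-adjusted (ANCOVA) difference between arms at months 6 and 15 with a two-sided 95% CI, and do not apply Bonferroni to these harm comparisons.
- Fix a margin before unblinding, in the same SD units as the estimate.
- Conclude 'not worse' only if the interval excludes the margin; otherwise write 'inconclusive'.
- If no margin can be agreed, drop the similarity claim and report the estimates with their intervals.

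Keep the difference test for attention, where a difference is expected. When interpreting, state that neither contrast matches time since ECT: at month 6 the short course is ending and the long one continues, and at month 15 the arms are about 9 and 3 months past treatment.

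The cost is wording in the analysis plan and agreement on a margin, with no extra patients or visits. The downside is that with 25 to 32 patients per arm the trial will often have to conclude 'inconclusive'.

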### Trial design {8}

This study is a prospective, multicentric, randomized, two-arm, assessor-blinded trial.

Due to the severity of the patients’ condition, it is not ethically possible to conduct sham ECT sessions, making the blinding about the short or long arm impossible to maintain in patients. In this superiority trial, patients will be randomly assigned to one of both arms with an allocation ratio of 1:1.

## Methods: participants, interventions, and outcomes

The protocol study follows the SPIRIT recommendations.

### Eligibility criteria {10}

Patients eligible for the study are patients with schizophrenia continuing to experience persistent psychotic symptoms despite a well-managed clozapine treatment.

#### Inclusion criteria

Patients aged 18 to 55Patients with schizophrenia as defined by the DSM-5 criteriaPatients had at least two previous unsuccessful treatment trials with conventional or atypical antipsychotics from two different classes at a dose of ≥600 mg chlorpromazine equivalentPatients had received clozapine for at least 6 weeks prior, with a plasma concentration ≥ 350 ng/mlPatients continuing to experience persistent positive psychotic symptoms with a score of at least 4 (moderate) on at least two of the four positive symptoms of the BPRS (grandiosity, suspiciousness, hallucinations, and unusual thoughts)Current presence of at least moderately severe illness, with total BPRS score ≥ 45 and a CGI-S score ≥ 4 (moderate)Patients had a stable treatment for at least 8 weeks (antipsychotics, mood stabilizers, and antidepressants)Patients affiliated to a social security systemPatients able to understand both spoken and written FrenchPatients giving their informed written consent and agreement of their legal guardian for patients under guardianshipPatients deprived of liberty if they gave their informed, written consent

#### Non-inclusion criteria

Patients with current depressive, manic, or hypomanic episodes as defined by the DSM-5 criteriaPatients who had ECT during the last 6 monthsPatients with unstable epilepsyPatients with a severe neurological or systemic disorder that could significantly affect cognition, behavior, or mental status (other than tardive dyskinesia or neuroleptic-induced parkinsonism)Patients with one or more of the following conditions (in order to minimize risks related to ECT and general anesthesia): intracranial hypertension, recent myocardial infarction, advanced coronary failure, embolic disease, recent stroke, the existence of expansive intracranial lesions without intracranial hypertension, the presence of aneurysms or cerebral vascular malformations with bleeding risk, aneurysm of the aorta, the existence of a retinal detachment, the existence of a pheochromocytoma, and serious heart or respiratory failurePatients with a severe substance use disorder (other than nicotine or caffeine) according to the DSM-5 criteriaPatients with concomitant use of benzodiazepines and antiepileptic drugs, except for lamotriginePregnant or lactating women and women of childbearing age without adequate contraceptionPatients with contraindications to etomidate or any of its excipients and/or neuromuscular blocking agentsPatients participating, or having participated within the 30 days prior to the inclusion visit, in an interventional clinical trial

#### Exit criteria

The patients are definitively excluded from the study in the following cases: removal of the patient’s consent or the legal guardian agreement (in these cases, the collected data are not included in the data analysis)Patients refusing to continue the study, without removal of the consent (in these cases, the collected data will be included in the data analysis)Decision of the investigator: worsened clinical condition, occurrence of significant adverse effects, need to change the background drug treatment, and impossibility for the patient to follow the established protocolDeath of the patient;Patient lost to follow-up (after unsuccessfully trying to contact the patient three times at 1-week intervals)

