#### Criteria for discontinuing or modifying allocated interventions {11b}

The patients stop participating in the study in the following cases:
Removal of the patient consent or the legal guardian agreement (in these cases, the collected data are not included in the data analysis)Patients refusing to continue the study, without removal of consent (patients’ data may be analyzed)Decision of the investigator: if the patient’s clinical condition worsens, significant adverse effects occur, wish of the patient to receive more ECT when he/she is assigned to the short arm, need to change the background drug treatment, impossibility for the patient to follow the established protocolDeath of the patient;Patients lost to follow-up (after unsuccessfully trying to contact the patient three times at 1-week intervals)

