### Outcomes {12}

#### Main outcome

The main outcome is the response rate assessed by the Positive and Negative Symptoms Scale (PANSS) 3 months after the end of the treatment in patients following the long protocol (i.e., at 15 months) compared to those following the short protocol (i.e., at 9 months), the response being defined as a 30% reduction on the PANSS [12].

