### Plans to promote participant retention and complete follow-up {18b}

No specific strategy is planned to promote participant retention. However, resistant schizophrenic patients are mostly long-term hospitalized patients because of their serious illness. Being hospitalized can guarantee adherence to care. As far as possible, if the patient wishes to stop ECT sessions, it is recommended to proceed to the next follow-up visit in order to have the most concomitant data of the end of the ECT.

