## Discussion

Even though ECT is recommended for patients with URS, there is a noticeable lack of rigorous studies on this subject. Parameters such as the frequency of ECT sessions, the position of electrode(s), the seizure efficacy criteria, or the anesthetic management have been little studied and should be tested. In addition, the utility of maintenance ECT in patients with URS has never been studied, except in open studies and clinical cases. The present study focuses on the optimal duration of ECT treatment, aiming to compare two protocols of combining ECT with clozapine: a 6-month protocol and a 12-month protocol.

The minimum number of ECT sessions to achieve significant clinical improvement in patients with URS ranges between 16 and 20 [49, 50]. In a recent meta-analysis about ECT augmentation of clozapine for clozapine-resistant schizophrenia, the mean duration of the included studies was only 8–9 weeks [4]. The authors suggested that longer-term follow-up data are needed in order to assess if patients maintain the clinical improvement that they achieved from ECT augmentation of clozapine, or whether maintenance ECT is required. The present study should try to answer this important question. We hypothesized that the long protocol will be more effective than the short protocol. It is important to accurately assess the efficiency gain because an increased duration of treatment leads to an additional cost and decreases the number of potentially treated patients. A long protocol could also allow a better stabilization of patients, avoid relapses and hospitalizations, and thus improve their cognitive profile and their quality of life.

Some methodological choices we made are worth discussing.

First, the duration of participation in this study is long (15 months in total). There is therefore a risk of having a significant number of patients lost to follow-up, especially in severely disabled patients. In the sample size calculation, the drop-out rate was estimated to 20% and the number of patients increased to overcome the reduction of statistical power. However, we lack data to accurately estimate this rate.

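### Three failed weekly contacts end study participation for good, with no way back for the primary PANSS at month 9 or month 15

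*Protocol article*

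**What the plan says.** The Exit criteria open with "The patients are definitively excluded from the study in the following cases", and one of those cases is "Patient lost to follow-up (after unsuccessfully trying to contact the patient three times at 1-week intervals". Section {11b}, on discontinuing or modifying the intervention, repeats the rule under "The patients stop participating in the study in the following cases", again naming "Patients lost to follow-up (after unsuccessfully trying to contact the patient three times at 1-week intervals". In both places the consequence is leaving the study, not only stopping ECT.

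The main outcome is PANSS response, read "3 months after the end of the treatment in patients following the long protocol (i.e., at 15 months") and at month 9 in the short arm.

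Section {18b} states: "No specific strategy is planned to promote participant retention". It adds that these patients are mostly in hospital long term, and it recommends going to the next follow-up visit when a patient wishes to stop ECT. The Discussion notes that "the duration of participation in this study is long (15 months in total") and continues: "There is therefore a risk of having a significant number of patients lost to follow-up". It also says that data to estimate the drop-out rate accurately are lacking.

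Section {20c} adopts intention to treat and handles patients not assessed 3 months after treatment by a maximum-bias rule. They count as non-responders in the arm doing better and as responders in the arm doing worse. Section {20c} names patients lost to follow-up as the group to which this applies.

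**The concern.** The primary outcome is a single assessment, often many months after the moment at which contact might fail. A silence of two to three weeks at month 3, for example, closes an outcome that is not due for another 6 months (short arm) or 12 months (long arm). If the patient is reached again in between, the assessment could be made, but under the rule as written the patient has already left the study.

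Nothing else in the article reopens that door. The provision in {18b} covers patients who wish to stop ECT, not patients who cannot be reached. Section {20c} then carries the exit rule straight into the primary analysis, because it takes lost-to-follow-up patients as the ones to impute. An obtainable outcome would be replaced by an assumed one chosen to shrink the treatment difference. That costs power and sits badly with the intention-to-treat principle that the same section states.

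**Working it through.** **Inputs.** Response rates 61.79% (long) and 23.25% (short), alpha 0.05, power 0.80, 25 per group raised to 32 for 20% drop-out: Sample size {14}. Pearson chi-square test: {20a}. Maximum-bias imputation: {20c}. The protocol does not state whether alpha is one- or two-sided; two-sided is assumed because it reproduces the plan's figure.

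**Step 1: the plan's own figure.** With pooled variance and no continuity correction, the mean rate is (0.6179 + 0.2325)/2 = 0.4252 and

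n = [1.96·√(2·0.4252·0.5748) + 0.8416·√(0.6179·0.3821 + 0.2325·0.7675)]² / 0.3854² = 24.6, so 25 per group.

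Then 25/0.80 rounds up to 32. Both stated figures reproduce.

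**Step 2: how one missing outcome acts.** Let m patients of 32 be missing in each arm, with missingness unrelated to response. If the long arm does better on the observed data, the expected analysed rates are

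- long: 0.6179·(32 − m)/32
- short: [0.2325·(32 − m) + m]/32

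At m = 6 (20% of 32 is 6.4) these are 50.2% and 37.6%, a gap of 12.6 points instead of 38.5.

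**Step 3: exact power.** I enumerated both binomials with 32 − m assessed per arm, applied the {20c} rule according to the observed direction, and tested with the Pearson chi-square at two-sided 5%. The complete-case column uses the same enumeration with missing patients left out.

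| Missing per arm, all causes | Power under {20c} | Power, complete case |
|---|---|---|
| 0 | 91% | 91% |
| 1 | 83% | 89% |
| 2 | 72% | 88% |
| 3 | 58% | 86% |
| 4 | 42% | 84% |
| 5 | 27% | 83% |
| 6 | 14% | 82% |

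**Step 4: value of a recovered outcome.** From unrounded values, each step between rows (one outcome recovered in each arm) is worth 7.4 points at the top of the table, 16.0 at most (from 4 to 3 missing), and 12.6 from 6 to 5. So the range under {20c} is about 7 to 16 points per pair. In the complete-case column each step is worth 0.2 to 1.9 points.

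**Step 5: what is not known.** The six per arm stand for all drop-out. The protocol does not say how many of them would be lost contacts, or how many of those would be reached again before the primary visit. That share can lie anywhere from 0 to 100%. If it is zero, changing the rule gains nothing. If one of six were recovered in each arm, power would rise from 14% to 27%; if two of six, to 42%. A short-arm patient lost after month 9 already has the primary outcome and is unaffected.

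**The case against.** The strongest reply is that the damage comes from the imputation in {20c}, not from the contact rule. This stands: without that imputation, recovering two of six outcomes per arm moves power only from 82% to 84%. The contact rule matters as much as it does because the plan's own primary analysis turns each loss into an adverse outcome.

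A second reply is that the 20% covers every exit: refusal, withdrawn consent, investigator decision, death and lost contact. This also stands. The fall from 91% to 14% cannot be charged to the contact rule alone, and 14% to 42% is an illustration, not an estimate. Long-stay inpatients are also unlikely to be out of reach for three weeks, so the number affected may be small.

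A third reply is that tracing procedures are detail which an article may leave to the full protocol. That is fair for the tracing routes. It does not cover the wording that is printed, which makes the exit definitive and appears in two sections.

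Three stronger readings are tempting and are not supported.

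- A reader might infer that the rule forbids contact through the ward, the treating psychiatrist or a guardian. It does not say how contact is to be tried; it ends participation without requiring those routes.
- A reader might infer that the sponsor expects many losses. The Discussion speaks of a risk and says the rate cannot be estimated well.
- A reader might infer that the rule unbalances the arms. The exposure of 9 versus 15 months before the primary visit follows from the endpoint timing, affects every kind of attrition, and would remain after this fix.

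**Conclusion.** The point holds as a badly fixed rule. As printed, three failed weekly contacts permanently end participation, and a patient reached again before month 9 or month 15 would not be assessed for the primary outcome. The plan would then impute a result it could have observed.

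The size depends on a number the protocol does not give. Under the {20c} imputation each recovered pair of outcomes is worth about 7 to 16 points of power; under complete-case analysis, 0 to 2 points. These figures assume 32 per arm, the planned response rates, equal numbers missing in the two arms, missingness unrelated to response, and a two-sided 5% test. The sample size arithmetic itself is correct. The change is worth making because it is cheap and because even one or two outcomes matter under the planned analysis, not because large losses have been shown.

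**What to change.** In the Exit criteria and in {11b}, take lost contact out of the cases that definitively end participation and record it as missed visits. Keep the remaining PANSS visits, above all month 9 (short arm) or month 15 (long arm), open to any patient who still consents and is reached again. Class a patient as not assessed for the primary outcome only after renewed attempts around that visit have failed, including through the ward, the treating psychiatrist or the guardian. State this in {18b} as the retention measure, so that {20c} imputes only outcomes that could not be obtained.

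The cost is a short amendment and a few extra calls for each patient out of contact. No treatment, scheduled visit or staffing changes.
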